## Abstract

**Background:**

Bilateral cerebral palsy (BCP) is the most common type of CP in children and is often accompanied by different degrees of communication impairment. Several studies have attempted to identify children at high risk for communication impairment. However, most prediction factors are qualitative and subjective and may be influenced by rater bias. Individualized objective diagnostic and/or prediction methods are still lacking, and an effective method is urgently needed to guide clinical diagnosis and treatment. The aim of this study is to develop and validate an objective, individual-based model for the prediction of communication impairment in children with BCP by the time they enter school.

**Methods:**

A multicenter prospective cohort study will be conducted in four Chinese hospitals. A total of 178 children with BCP will undergo advanced brain magnetic resonance imaging (MRI) at baseline (corrected age, before the age of 2 years). At school entry, communication performance will be assessed by a communication function classification system (CFCS). Three-quarters of children with BCP will be allocated as a training cohort, whereas the remaining children will be allocated as a test cohort. Multivariate lesion- and connectome-based approaches, which have shown good predictive ability of language performance in stroke patients, will be applied to extract features from MR images for each child with BCP. Multiple machine learning models using extracted features to predict communication impairment for each child with BCP will be constructed using data from the training cohort and externally validated using data from the test cohort. Prediction accuracy across models in the test cohort will be statistically compared.

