### Study Procedures

The study procedures are shown in Figure 1. Following the inclusion and exclusion criteria, eligible participants (children with BCP and PWMLs) will be entered from corrected ages of 6 to 24 months. Participants will be assessed for diagnostic criteria, differential diagnosis and comorbidities by a pediatrician or child neurologist. The participants will undergo at least 1 advance brain MRI examination according to a standardized protocol. A variety of clinical data and data pertaining to socioeconomic status will be collected. Neurobehavioral development will be assessed by experienced physiotherapists blinded to the MRI findings and related medical information (such as other examination results relevant to the content of the current assessment) at each center.

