**FIGURE 2 F2:**
[figure not shown]
Data processing and analysis workflow. **(A)** First, the lesion will be manually defined on T_2_-FLAIR images. **(B)** Two complementary methods, one based on lesions and the other on the connectome, will be used to characterize brain damage. To compute lesion-based damage (top row), the brain atlas and each individual’s lesion mask will be aligned with each individual’s native T_1_ space. The gray matter regions will be divided into regions of interest (ROIs) according to the atlas. Then, lesion-based damage will be computed as the proportion of lesioned voxels per ROI based on the lesion mask. Connectome-based damage (bottom row) will be computed as the number of diffusion tensor imaging (DTI) tracts that connect each pair of ROIs (tractography for reconstructing tracts will be performed guided by the white matter probabilistic map). **(C)** For each individual, three feature sets (lesion features, connectome features, and combination features) will be generated from the corresponding features after feature selection. **(D)** For each feature set, a “training cohort” will be used to build an optimal model based on a 10-fold cross-validation, and the prediction performance of the optimal model will be tested with the “test cohort” using ROC curve. **(E)** Then, three optimal models will be generated based on different feature sets (the lesion feature set for voxel model, the connectome feature set for connectome model, and the combination feature set for combination model). The prediction performance of each model will be compared, and the best-performing model will be selected.

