Images from four sites (four hospitals) will be randomly partitioned into four equal portions. Approximately three-quarters of these images will be used as a “training cohort,” and the remaining one-quarter of these images will be used as a “test cohort.” In the “training cohort,” the proportion of lesioned voxels in the ROI and the links of the connectome matrix that are not shown difference between absence of communication impairment group and communication impairment group will be excluded, where the significance level is defined as *P* < 0.05 without multiple comparison correction in the two-sample test. The selected features will be used to define models predicting presence or absence of communication impairment in children with BCP. For each prediction model, 10-fold cross-validation (CV) will be used to evaluate the performance. This means that the “training cohort” will be divided into a training (nine folds) and a validation dataset (one fold), leaving 9 of 10 participants in the training dataset and the remaining participants in the testing dataset. For the training cohort, the various hyperparameters within each algorithm will be used to determine the prediction model. Then, the model will be applied to the validation dataset to predict children with the presence or absence of communication impairment (predicted label). The same procedure will be repeated with each of the one-fold participants or the left-out participants in the leave-one-out procedure, serving as the validation dataset for 10 iterations. Thus, each subject will receive a predicted label, and the accuracy of predictive model will be evaluate by comparing predicted labels to true labels of BCP children. The CV step will be repeated 100 times with random cohort designation to select the model with the best prediction accuracy. The whole “training cohort” will be reused in its entirety to retrain the model based on the classification algorithm and hyperparameters of the prior selected model. Then, the retrained model will be used to evaluate the “test cohort,” and the communication performance of every subject of the “test cohort” will be predicted by the model. The final accuracy of the prediction model will be defined by comparing predicted labels to true labels of BCP children in the “test cohort,” The Receiver Operating Characteristic (ROC) curve and the area under curve (AUC) will be calculated to evaluate the predictive ability of built models. A two-sided Hotelling-Williams test (Steiger, 1980) will be used to determine whether the multimodality prediction model is more accurate than any of the single-modality prediction models. *P* values < 0.05 will be considered indicative of statistically significant differences across models. Given the possible effects of age on imaging measures, the “test cohort” will be divided into three groups: younger (6–12 months), middle-aged (12–18 months), and elderly (18–24 months years), according to their age at MRI scan. The optimal model will be applied to all subgroups to exam whether the prediction accuracy changes with age at MRI scan.

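### The test cohort is an internal split-sample hold-out, not an external validation, and choosing the best of three feature-set models on it makes the winner's reported performance optimistic

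*Protocol article*

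**What the plan says.** **Label.** The abstract's Methods paragraph says that the models will be "externally validated using data from the test cohort".

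**How the cohort is formed.** Development and Validation of Prediction Models states: "Images from four sites (four hospitals) will be randomly partitioned into four equal portions". About three-quarters form the training cohort, and "the remaining one-quarter of these images will be used as a" test cohort. No hospital, calendar period or separate population is held back.

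**Choices made in training.** The same section runs 10-fold cross-validation within the training cohort: "The CV step will be repeated 100 times with random cohort designation to select the model with the best prediction accuracy". The chosen algorithm and hyperparameters are then refitted on the whole training cohort.

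**Choices made after that.** The Figure 2 legend, part D, says for each feature set that "the prediction performance of the optimal model will be tested with the" test cohort. Part E says that "three optimal models will be generated based on different feature sets" and then: "The prediction performance of each model will be compared, and the best-performing model will be selected". The abstract confirms that the comparison across models is made in the test cohort. The body text defines final accuracy in that cohort and applies the optimal model to its three age groups.

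**The concern.** There are two separate problems.

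1. **The label.** External validation means testing on children from a source that played no part in development. A random split pooled over sites puts the same hospitals, scanners and assessors on both sides. The Harmonization section treats site differences as a real threat and removes them with ComBat, which adjusts each site's mean and variance from that site's data. Transport to a new hospital is therefore not measured, although the label suggests that it is. The limitations in the Discussion restrict generalisability to other CP subtypes and imaging findings, but do not mention other hospitals.

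2. **Selection and scoring on the same children.** If three models are scored on one small cohort and the highest is kept, its score contains the luck that made it highest. No further untouched data are described, so nothing corrects for this.

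The Primary Aim is to develop and validate a model, so both problems bear on the headline result.

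**Working it through.** **1. The two descriptions side by side.**

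| Feature | Abstract | Development and Validation section |
|---|---|---|
| Name or method | external validation | random partition |
| Source of test data | not stated | the same four hospitals, pooled |
| Hospital held out | not stated | none |

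The second column describes split-sample internal validation.

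**2. Size of the test cohort.** The Sample Size section uses f² = 0.10, 6 predictors, α = 0.05 and power 0.80. The overall F test with noncentrality f²·N and degrees of freedom 6 and N − 7 first reaches 0.80 at N = 143 (power 0.801), which reproduces the plan's figure. One quarter is 143/4 = 35.75, about 36 children. With no dropout it is 178/4 = 44.5.

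**3. Precision at that size.** I assume 47% impaired, the prevalence quoted in Sample Size: 0.47 × 36 ≈ 17 impaired and 19 unimpaired. The Hanley-McNeil 95% half-width is about ±0.17 for a true AUC of 0.70 and ±0.15 for 0.80.

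**4. Optimism of the selected model.** Define optimism as E[observed AUC of the selected model − true AUC of that model]. Scores are simulated as correlated normals, shifted in the impaired group by √2·Φ⁻¹(AUC), with 17 and 19 children. The model with the highest observed AUC is kept. True AUCs and correlations are assumptions, because the protocol gives none.

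| True AUCs | Score correlation | Optimism |
|---|---|---|
| 0.70, 0.70, 0.70 | 0.3 | +0.064 |
| 0.70, 0.70, 0.70 | 0.5 | +0.054 |
| 0.70, 0.70, 0.70 | 0.7 | +0.043 |
| 0.70, 0.70, 0.70 | 0.9 | +0.025 |
| 0.65, 0.70, 0.75 | 0.3 to 0.7 | +0.05 to +0.03 |
| 0.70, 0.70, 0.78 (combination best) | 0.8 with each single model | about +0.017 |
| 0.65, 0.70, 0.78 (combination best) | 0.8 with each single model | about +0.011 |

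Across these scenarios the range is about 0.01 to 0.06. With true AUCs of 0.65, 0.70 and 0.75, a model other than the truly best one is selected in roughly 30% to 40% of runs.

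**5. Cross-check on accuracy.** Three equally accurate models (true accuracy 0.70 to 0.80, latent correlation of correctness 0 to 0.9) on 36 children give a best-of-three overstatement of 3.0 to 6.4 percentage points. On 44 children it is 2.8 to 5.8 points.

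**The case against.** **Most of the tuning is sound.** Algorithm and hyperparameters are picked inside the training cohort. Only the choice among three pre-defined feature sets uses test data. That stands, and it limits the bias to a best-of-three effect.

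**Selection is stated only in a figure legend.** The body text describes a test of the multimodality model against the single-modality models, and nothing says that only the winner is reported. A reader might infer that all reported test performance is biased. The documents do not support that: each model's own result is unbiased by selection if all three are shown without a winner's claim. But the legend does commit to selecting one, and the figure then quoted for that model is affected.

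**The size depends on assumptions.** The combination model contains the other two feature sets, so equal performance with low correlation is an unfavourable case. If the combination is truly better, optimism falls to about 0.01 to 0.02. Sampling error (SD of one AUC about 0.08 to 0.09) exceeds the bias throughout. This stands and sets the lower end of the range. The bias nevertheless runs in one direction, and an ordinary confidence interval does not correct it.

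**A child in both cohorts.** The split is worded in terms of images, and Study Procedures says: "The participants will undergo at least 1 advance brain MRI examination according to a standardized protocol". A reader might infer that one child could fall on both sides. The documents do not support this as a finding. The abstract allocates children, the preselection section gives each subject one set of features of each kind, and the validation text counts participants and subjects. Nothing has a child contributing twice, so the wording is loose and does not show leakage.

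**Scope of the external claim.** The word occurs once, in the abstract, and the Primary Aim does not use it. The tools are described only as a possible later result. This makes the correction small, but the statement is still wrong.

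**Conclusion.** The concern holds in two limited respects. First, the abstract's external-validation label contradicts the protocol's own split; the evaluation is internal, and performance at an unseen hospital is not estimated. Second, selecting among the lesion, connectome and combination models on the test cohort, and taking final accuracy from the same cohort of about 36 children, makes the selected model's figure optimistic by roughly 0.01 to 0.06 in AUC. That range rests on assumed true AUCs of 0.65 to 0.78, score correlations of 0.3 to 0.9 and 47% impairment. The first point is certain from the text. The direction of the second is also certain if the legend is followed, but its size is not. The age-subgroup results for the optimal model come from the same selected-on data.

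**What to change.** 1. In the abstract, replace the external-validation wording with internal (split-sample) validation, and add to the limitations that performance at other hospitals is untested.
2. In the Figure 2 legend, part E, and in Development and Validation of Prediction Models, state that one final model, including its feature set, is chosen by cross-validation in the training cohort and fixed before the test cohort is opened. Its test result is the headline figure. The other two models' test results are secondary comparisons and do not change the choice.
3. For that choice to be fair, rerun the two-sample P < 0.05 filter inside each cross-validation fold. With 122 regions there are up to 122 × 121/2 = 7,381 links against at most 122 lesion proportions, so a filter applied once to the whole training cohort would flatter the connectome set more.
4. Optionally, add leave-one-hospital-out performance as a sensitivity analysis. It is the only element that would address transport between hospitals. It should not replace the main plan without more information: site sizes are not stated, and a held-out site cannot be ComBat-corrected from training data.

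**Cost.** Items 1 to 3 need text changes and some re-coding, but no extra children or scans. The headline accuracy may be slightly lower, and no external-validity claim can be made.

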**Discussion:**

The findings of the study may lead to the development of several translational tools that can individually predict communication impairment in children newly diagnosed with BCP to ensure that these children receive early, targeted therapeutic intervention before they begin school.

**Trial registration:**

The study has been registered with the Chinese Clinical Trial Registry (ChiCTR2100049497).

## Introduction

Cerebral palsy (CP) is the most common physical disability in childhood and occurs in 2–3 per 1,000 live births (Patel et al., 2020). Recently, the majority of individuals with CP achieve a life expectancy close to that of the general population. Clinical and research interests now focus on improving the ability of children with CP to perform activities of daily living and socially interact. Communication plays an integral role in people’s daily activities and social participation, yet only a few studies have examined the prevalence and features of communication impairment in children with CP (Mei et al., 2016; Kristoffersson et al., 2020). Communication (receptive and/or expressive language) impairments are common comorbidities in patients with CP, with a prevalence ranging from 46 to 78% (Coleman et al., 2015, 2016; Mei et al., 2016; Kristoffersson et al., 2020). Communication problems result in poor prospects of engagement and social participation in children with CP across a range of activities, including self-development, social functioning, and learning (Pennington et al., 2019; Vaillant et al., 2020). Particularly by the time these children enter school, communication skills greatly impact school readiness, which affects later social and academic success as well as economic and health outcomes (High, 2008).

Language development from birth to 2 years, when brain plasticity is at its greatest, presents multiple opportunities for intervention (Chorna et al., 2017). During this period, language perception (receptive) and production (expressive) are accompanied by the development of cortical areas responsible for improvements in working memory and pattern recognition in the first year and the multiplication of associations between different cortical processing areas in the second year (McMahon et al., 2012). Social interactions and interventions leveraging cortical development and cortical associations between language and motor systems at this critical time represent a promising role in improving long-term language outcomes and social functions (Goldstein et al., 2003; McMahon et al., 2012; Lipscombe et al., 2016; Chorna et al., 2017). Therefore, the key to interventions in these individuals lies in the importance of the early identification of children with CP at high risk for communication impairments (Coleman et al., 2015).

Several studies (Coleman et al., 2015; Hustad et al., 2018; Pennington et al., 2020; Tan et al., 2020) have attempted to explore demographic variables, early clinical characteristics, and environmental factors in predicting communication ability in children with CP at school entry. Studies have demonstrated that communication, cognition, and motor performance at an early age are critical for predicting future functional communication in children with CP (Coleman et al., 2015; Hustad et al., 2018; Pennington et al., 2020; Tan et al., 2020). However, most standardized tests require behavioral repertoires that exceed the capabilities of young children with CP, which makes these measures too difficult to use to assess these children reliably (Geytenbeek et al., 2010; Nordberg, 2018). Other non-standardized tests, such as parent-completed measures and grade-level classification systems, are unlikely to easily and adequately capture the scope of information necessary to track impairment-related changes (Geytenbeek et al., 2010; Potter, 2016). All these limitations make these methods less accurate in identifying or predicting children with CP at high risk for communication impairment.

In recent decades, progress in magnetic resonance imaging (MRI) techniques has increased the number of opportunities to search for more precise and objective biomarkers in various pediatric neurological diseases; additionally, MRI has been recommended and widely used for diagnosis, prognosis, treatment monitoring and research in CP (Graham et al., 2016; Novak et al., 2017). Three studies (Geytenbeek et al., 2015; Coleman et al., 2016; Choi et al., 2017) used qualitative categorical descriptions from MRI to investigate the characteristics of brain abnormalities associated with communication performance in children with CP. All these studies found that communication is related to the type of brain lesion on MRI (qualitative measurement); specifically, more severe periventricular white matter lesions (PWMLs) are associated with worse communication performance for the patient. Moreover, some researchers (Coleman et al., 2016; Laporta-Hoyos et al., 2018) used a semiquantitative MRI scale that provides scores by evaluating the extent of brain injury—assigning higher scores for increased lesion involvement—to assess the severity of brain damage in children with CP. The results demonstrated that children with CP with more severe lesions in the presumed language pathway regions (the left frontal, left temporal, left thalamus, left posterior internal capsule, left caudate and lenticular nuclei) had poorer overall communication skills and lower Communication and Symbolic Behavior Scales Developmental Profile (CSBS-DP) total scores (Coleman et al., 2016). All these results indicate that MRI has potential value in predicting communication impairment in children with CP. However, the above studies had a cross-sectional design, and variables reported as risk factors were qualitative or semiquantitative. Thus, an early quantitative and individualized prediction model for communication outcomes based on patient characteristics and MRI parameters is still lacking.

Multivariate lesion- and connectome-based approaches (Gleichgerrcht et al., 2017) are emerging techniques that provide an objective and quantifiable way to statistically evaluate the relationship between whole-brain structure connections and behavioral function. Notably, a prediction model constructed from this approach had high efficacy in the prediction of language deficits in post-stroke patients (Yourganov et al., 2016) and motor outcomes in neonates with arterial ischemic stroke (Al Harrach et al., 2021). Therefore, this study aims to develop individual prediction models based on multivariate lesion- and connectome-based approaches at an early age to predict communication ability in children with CP by the time they enter school. Among all types of CP, bilateral cerebral palsy (BCP) is the most common subtype, comprising 64.7% of all cases (Colver et al., 2014). Furthermore, different neuroimaging findings have revealed different patterns of insult to the brain in CP; recent research has noted that white matter lesions are the most common findings in imaging, accounting for 49.1% of all cases, and the severity of PWMLs has been verified to be linked with communication performance in children with CP (Geytenbeek et al., 2015; Coleman et al., 2016; Choi et al., 2017). Thus, we will also limit study participants to those with BCP and PWMLs (the most common subtype and neuroimaging finding in children with CP) to reduce the heterogeneity within the study population to improve the accuracy of prediction models. The results of this study may lead to the development of several translational tools that can be used to make individualized predictions of communication impairments in children newly diagnosed with BCP and PWMLs to ensure that these children receive early, targeted therapeutic intervention before they begin school.

